The number of days of psychiatric hospital treatment, as well as quantity and dosage of medication and the number of psychotherapy sessions, will be recorded. Furthermore, critical stress-related events after discharge and the subjective degree of stress will be collected.

Basic descriptive data on regional health care services/differences at the four participating hospitals will be collected (e.g., number of patients presenting with disorders of F2 and F3-section (ICD-10), regional characteristics, differences in networks of psychiatric support, and treatment after discharge). Recruitment started in 2018 and will end in 2021.

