### Course

All patients receive a baseline visit (V0) during the week prior to discharge. At the baseline visit, data on demographics, substance use, psychiatric and medical history and treatment, history of suicidality, and family history of suicidality are documented.

In group 1, study contacts are scheduled at 6 (V6), at 12 (V12), and at 18 (V18) months after discharge from the psychiatric hospital. In group 2, more frequent study contacts are organised: During a period of 6 months after discharge, study visits are scheduled monthly (V1–V6), and subsequently every 2 months during the next period of 6 to 18 months after discharge (V8–V18). There will be a total of 3 study visits in group 1 and 12 study visits in group 2. The protocol (Fig. 1) accepts flexibility in terms of time, plus/minus 1 week, for study visits in the first 6 months after discharge, as well as a plus/minus 2 weeks tolerance for study visits V8 to V18. In case a patient gets admitted to a hospital while participating in the study, the course will be continued as conducted. Study visits include an evaluation of events that occurred between the study visits, e.g., stress-related events, inability to work, days of inpatient treatment, change or discontinuation of any treatment, and change of doctors, or therapists. Both baseline and study visit additionally includes several assessments recording symptomatology described in the next section.

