### Statistical analysis

Descriptive statistics covering sociodemographic and clinical baseline data will be reported using proportions, means, and standard deviations as well as Chi-square tests, *t* tests, and Mann-Whitney tests as appropriate. Results will be presented with 95% confidence intervals where applicable. Proportions of adverse events will be summarised. Sociodemographic and clinical variables that differ significantly between groups at baseline will be included as covariates in further analyses. To identify potential explanatory variables on suicidality in the weeks and months after discharge, a potential correlation of variables will be assessed by frequencies, percentages, means and standard deviations, correlation coefficients, etc. Variables that are identified as potentially influencing suicidality will be included as factors in further analyses.

Normal distribution will be assessed by Shapiro-Wilk tests and by visual inspection of histograms. Homogeneity of variances will be assessed using Levene’s test.

Statistical tests will be two-sided using an alpha level of 0.05. All analyses will be conducted using IBM SPSS Statistics for Windows, version 25.

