#### Primary outcome measures

Group comparison of suicidality measured by the score of the clinician-administered Sheehan Suicidality Tracking Scale will be conducted using analysis of covariance (ANCOVA). Baseline variables that differed significantly between groups, as well as potentially influencing risk factors, will be included in the analysis.

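### The covariate rule for the primary ANCOVA does not exclude variables measured after the contacts begin, so it can remove part of the group effect or create a spurious one

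*Protocol article*

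**What the plan says.** The section Statistical analysis describes the screen: "To identify potential explanatory variables on suicidality in the weeks and months after discharge, a potential correlation of variables will be assessed". It then fixes what happens to the variables found: "Variables that are identified as potentially influencing suicidality will be included as factors in further analyses".

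The section Primary outcome measures applies this to the ANCOVA of the clinician-administered S-STS: "Baseline variables that differed significantly between groups, as well as potentially influencing risk factors, will be included in the analysis". The risk factors are listed as a second class beside baseline variables. Neither section gives a list or a screening threshold, or says when a variable must have been measured.

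Several variables gathered for the risk-factor question arise after discharge. Methods/design says that "critical stress-related events after discharge and the subjective degree of stress will be collected", and in the same place provides for recording "The number of days of psychiatric hospital treatment, as well as quantity and dosage of medication and the number of psychotherapy sessions". According to Course, the study visits ask about what happened since the last visit, including "days of inpatient treatment, change or discontinuation of any treatment, and change of doctors, or therapists".

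Other candidates are measured at V0. Course lists psychiatric history, history of suicidality and family history. Patient-administered scales lists the perfectionism questionnaire, the FPI-R and the RS13.

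**The concern.** A covariate in a group comparison should not itself be changeable by group. Here several candidates can be. Course lets the investigator coordinate further care with the treating psychiatrist or psychotherapist after a severe event, or bring the patient to a psychiatrist on site. The Discussion names earlier recognition of suicidal tendencies and the link to outpatient care as ways in which the contacts may work. Readmission, treatment change and therapy use are therefore plausible steps between the contacts and the S-STS score.

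Recording differs too. Group 1 is asked about six-month intervals at 3 visits, group 2 about one- or two-month intervals at 12 visits. Recorded events can then differ by group even where true events do not.

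Two errors can follow:
- Adjusting for a variable through which the contacts act removes that part of the effect.
- Adjusting for a variable driven both by group and by unmeasured severity can produce a group difference where there is none.

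In addition, covariates are chosen by their correlation with the outcome that the ANCOVA then tests, so the primary model depends on the outcome data.

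**Working it through.** The article states no power, effect size or error rate for this comparison, so there is no figure to reproduce.

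**From the article.** The target is at least 100 patients in each of four centres, 4 × 100 = 400. Alpha is 0.05, two-sided. Patients choose their group, so the split is unknown; contact-group shares of 50% and 25% were tried.

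**Assumed.** G is the contact group, B baseline S-STS, M one post-discharge variable and U unmeasured severity. B, U and both error terms are independent with SD 1:
- M = aG + uU + error
- Y = dG + bM + 0.5B + uU + error

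Effects are in units of the error SD of Y. Each scenario was simulated 4,000 times, comparing Y on G and B with Y on G, B and M. Confounding by patient choice was left out, to isolate the effect of adding M.

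**Case 1: M lies on the path (u = 0, b = 0.5).** The total effect is d + ab, set to -0.30. With M in the model the group coefficient is d.

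| Share mediated | a | d | Estimate with M | Power without → with M (50% share) | Same (25% share) |
|---|---|---|---|---|---|
| 25% | -0.15 | -0.225 | -0.22 | 0.77 → 0.59 | 0.64 → 0.49 |
| 50% | -0.30 | -0.15 | -0.15 | 0.75 → 0.31 | 0.64 → 0.27 |
| 100% | -0.60 | 0 | 0.00 | 0.75 → 0.05 | 0.64 → 0.05 |

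Hand check of the 50% row, equal groups:
- Without M, the residual SD is √(1 + 0.5²) = 1.118 and the SE is 2 × 1.118/√400 = 0.112. Then 0.30/0.112 = 2.68, and power is Φ(2.68 - 1.96) = 0.76.
- With M, the SE is (2/√400) × √(1 + 0.30² × 0.25) = 0.101. Then 0.15/0.101 = 1.48, and power is Φ(1.48 - 1.96) = 0.32.

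Both agree with the simulation. M correlated with Y at p < 0.05, and so would pass such a screen, in every run.

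**Case 2: no effect on Y, and M shares a cause with Y (d = b = 0, a = ±0.5).** With M in the model the group coefficient is -a·u²/(1 + u²). The correlation of M and Y given group and baseline is u²/(1 + u²).

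| u | u²/(1 + u²) | False effect, 0.5 × that | Type I error (50% share) | Type I error (25% share) | M passes screen |
|---|---|---|---|---|---|
| 0.3 | 0.09/1.09 = 0.08 | 0.04 | about 0.06 | about 0.055 | about 30% |
| 0.5 | 0.25/1.25 = 0.20 | 0.10 | about 0.14 | about 0.12 | about 95% |
| 0.8 | 0.64/1.64 = 0.39 | 0.20 | about 0.37 | about 0.29 | 100% |

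The simulated false effects match the formula. The direction depends on a: contacts that raise M look beneficial, and contacts that lower M look harmful. The type I errors are for a model that always contains M; in the weak scenario the screen would often leave it out.

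**Without M.** The model with group and baseline only recovers about -0.30 in case 1 and rejects in 0.044 to 0.054 of runs in case 2.

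**The case against.** Four arguments weigh on the other side.

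1. **The time phrase.** A reader might infer that the screen is aimed at variables arising in the weeks and months after discharge. The sentence does not support this: the phrase most naturally dates suicidality, the outcome. The point does not depend on it, because the rule has no timing limit under either reading.

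2. **Baseline risk factors.** A reader might also infer that the article names post-discharge events or treatment as covariates. It does not. The V0 questionnaires and the history of suicidality fit the term risk factor at least as well, and the two classes in the primary ANCOVA could differ by reason (imbalanced versus prognostic) and not by timing. This stands as a possible intention. It does not stand as a rule, because nothing keeps post-discharge variables out, and the Background lists new problems after discharge and poor adherence among the suspected causes.

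3. **Pilot and condensed article.** The study is self-selected and unpowered, risk factors are its first objective, and an exact covariate list may be left to an analysis plan. Adjustment for V0 risk factors is indeed needed when patients choose their group. But the article states a selection rule for the primary comparison, and Methods/design poses a test for a significant reduction. The objection is to that rule, not to a missing list.

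4. **Assumed magnitudes.** This stands in full. The weakest shared-cause scenario is close to the nominal error rate. Nor was the effect of choosing V0 covariates by their correlation with the outcome computed, so the inference that every p-value and interval would be invalid is not supported.

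**Conclusion.** The concern holds as a fault in a stated rule. Read together, the two analysis sections select covariates for the primary ANCOVA by their correlation with the outcome and do not restrict them to variables measured before the contacts begin. Followed as written, this can remove part of the effect under test or create one. It is not certain to do either: that depends on which variables are selected and how strongly they are tied to group and to severity.

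Under the assumed paths with equal groups, the estimate of a -0.30 SD effect falls to between -0.22 and 0.00, with power falling from about 0.76 to between 0.59 and 0.05. With no true effect, type I error lies between about 0.06 and 0.37. These are illustrations, not forecasts. The dependence of the primary model on outcome data is a further weakness, stated here without a size.

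**What to change.** In both Statistical analysis and Primary outcome measures, state that the primary group comparison adjusts only for variables measured at or before V0, taken from a list fixed before any outcome data are examined. The article contains no such list, so it has to be written. Candidates are baseline S-STS, history of suicidality, diagnosis, and the V0 questionnaires on perfectionism, personality and resilience.

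Move post-discharge hospital days, medication, psychotherapy sessions, treatment or therapist changes and stress events to a separate exploratory model for the first research question, or analyse them as outcomes or mediators. Make no claim about the group effect from the exploratory model.

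If only baseline risk factors were meant, one clause saying so in each section settles the timing; the list still has to be fixed in advance.

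The cost is plan wording and one additional model. No further data or patients are needed.

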### Study population and eligibility

Patients will be recruited from the four participating psychiatric hospitals in Germany (Department of Psychiatry and Psychotherapy, University Hospital Carl Gustav Carus, Dresden; Municipal Hospital Dresden, Department of Psychiatry and Psychotherapy, Dresden; Department of Psychiatry, Psychotherapy and Psychosomatics University Hospital Halle; Department of Psychiatry and Psychotherapy Furtbach Hospital, Stuttgart). All patients meeting the inclusion criteria will be informed about the study. Inclusion criteria are 18 years of age and older, admitted as an inpatient, presenting with either a mood/affective disorder (F3 section of ICD-10) or schizophrenia, schizotypal or delusional disorder (F2 section of ICD-10) and written informed consent. Patients agreeing to participate in the study have a choice to which group they want to belong to. A randomised allocation is not made for ethical reasons. Patients with legal guardians are excluded from the study. Patients are not given any incentive or compensation for participation.

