### Assessments

#### Clinician-administered scales

Sheehan Suicidality Tracking Scale (S-STS, [20]) is used to assess suicidal thoughts and/or behaviour, both clinician and self-reported. Items of the S-STS are scored on a 5-point Likert scale (0 = not at all, 1 = a little, 2 = moderately, 3 = very, and 4 = extremely). The Montgomery Asberg Depression Rating Scale (MADRS, [16]) will assess depressive symptoms; the Brief Psychiatric Rating Scale (BPRS, [17]) assesses psychotic symptoms. Investigators will also make use of the AMDP-rating scale to evaluate clinical psychopathology (Arbeitsgemeinschaft für Methodik und Dokumentation in der Psychiatrie, AMDP [19]). A rater training, as well as an evaluation of inter-rater reliability, was held at the beginning of the study to minimise differences between investigators and centres.

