#### Secondary outcome measures

Group comparisons of secondary outcome measures will be conducted using analysis of (co)variance (AN(C)OVA), Poisson regression, logistic regression, *t* tests, Chi-square tests, or non-parametric methods as appropriate. The course of suicidality measured with S-STS, as well as scores of the other scales, will be analysed within groups using repeated measures AN(C)OVA for both groups separately comparing baseline values with scores at 6, 12, and 18 months.

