The present study has several limitations. First, patients with a principal diagnosis of only categories F2 and F3 of ICD-10 (schizophrenia, schizotypal or delusional disorders, depression, bipolar disorder) will be included. In contrast, all other diagnoses will be accepted as comorbidities only. This procedure leaves out several groups of patients. We tried to restrict the heterogeneity of our study population in favour of receiving insights that are more meaningful for a well-defined group of patients at this first step of approaching very critical aspects of suicidality. Second, a bias may arise from the fact that patients have a choice of which group they would like to be placed in, either group 1 or group 2. On the other hand, this choice can offer useful insights into real-world clinical aspects by reflecting patients’ different characteristics as well as needs and motivation to make use of suicide prevention measures providing personal contact. This is in line with the ethical requirements of not withholding any condition from participants.

As a limitation of our study, we do not examine developments during the first days after discharge. The first study contact is scheduled 1 month after discharge. A recently published meta-analysis comprising 34 publications showed a pooled estimate of the suicide rate of 2950 suicides per 100,000 person-years (95% CI = 1740–5000) [28]. The pooled estimate of the suicide rate during the first month after discharge was 2060 per 100,000 person-years (95% CI = 1300–3280).

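### The primary ANCOVA pools one residual variance, with no stated consequence of the Levene check; if the self-chosen groups differ in both size and spread, its standard errors, intervals and p-values are miscalibrated

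*Protocol article*

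**What the plan says.** All references are to the protocol article.

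- Primary outcome measures: the group comparison of the clinician-administered S-STS "will be conducted using analysis of covariance (ANCOVA", adjusted for baseline variables that differ significantly and for potential risk factors. No other method is named.
- Statistical analysis: "Normal distribution will be assessed by Shapiro-Wilk tests and by visual inspection of histograms". "Homogeneity of variances will be assessed using" Levene's test. Neither check is followed by a stated action. "Statistical tests will be two-sided using an alpha level of 0.05", and 95% confidence intervals are promised where applicable.
- Secondary outcome measures: several methods are listed, ending "or non-parametric methods as appropriate". That latitude is written for secondary outcomes only.
- Study population and eligibility: "Patients agreeing to participate in the study have a choice to which group they want to belong to".
- Power analysis and sample size calculation: the target is at least 100 patients per centre, with no target per group.
- Clinician-administered scales: "Items of the S-STS are scored on a 5-point Likert scale", running from 0 to 4, so the score has a floor at zero.

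**The concern.** A classical ANCOVA estimates one residual variance for both groups. This is safe if the groups are of similar size or if their residual variances are equal. The design secures neither condition.

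On size, patients pick between a schedule of 3 study visits and one of 12, and the article sets no ratio or cap. On spread, scores near a floor of zero are compressed, so a group at a higher level will often vary more. The Discussion says the choice may reflect patients' "different characteristics as well as needs and motivation to make use of suicide prevention measures", which makes a difference in level plausible.

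If the smaller group varies more, the pooled standard error is too small, confidence intervals are too narrow and false positives are too frequent. If the larger group varies more, intervals are too wide and power is lost. Which case applies depends on a split the trial does not control.

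**Working it through.** **Inputs from the article.** Two-sided alpha is 0.05, so the critical value is 1.96. Four centres at 100 patients each give 4 × 100 = 400. There is no power or sample size figure to reproduce, because the article says none was calculated.

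**Inputs not in the article (assumed).** The splits are 50/50, 60/40 and 80/20. The ratio of residual SDs is 1.25 or 1.5, in either direction.

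**Formulae**, for sizes n1, n2 and residual SDs s1, s2:

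- pooled variance: sp² = (n1·s1² + n2·s2²)/N
- model-based: SE_model² = sp²·(1/n1 + 1/n2)
- actual: SE_true² = s1²/n1 + s2²/n2
- R = SE_model/SE_true, and true size = 2·[1 − Φ(1.96·R)]

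**60/40, smaller group more variable** (n1 = 160, s1 = 1.5; n2 = 240, s2 = 1):

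- sp² = (160 × 2.25 + 240)/400 = 1.5
- SE_model² = 1.5 × (1/160 + 1/240) = 0.01563
- SE_true² = 2.25/160 + 1/240 = 0.01823
- R = √(0.01563/0.01823) = 0.926, 1.96·R = 1.815, size = 7.0%

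**60/40, larger group more variable** (s1 = 1, s2 = 1.5):

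- sp² = (160 + 240 × 2.25)/400 = 1.75
- SE_model² = 0.01823, SE_true² = 1/160 + 2.25/240 = 0.01563
- R = 1.080, 1.96·R = 2.117, size = 3.4%

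**80/20, smaller group more variable** (n1 = 80, s1 = 1.5; n2 = 320, s2 = 1):

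- sp² = (80 × 2.25 + 320)/400 = 1.25
- SE_model² = 1.25 × (1/80 + 1/320) = 0.01953
- SE_true² = 2.25/80 + 1/320 = 0.03125
- R = 0.791, 1.96·R = 1.550, size = 12.1%

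**All cases:**

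| Split | SD ratio | Smaller group more variable: R, size | Larger group more variable: R, size |
|---|---|---|---|
| 50/50 | any | 1.000, 5.0% | 1.000, 5.0% |
| 60/40 | 1.25 | 0.957, 6.1% | 1.045, 4.1% |
| 60/40 | 1.5 | 0.926, 7.0% | 1.080, 3.4% |
| 80/20 | 1.25 | 0.876, 8.6% | 1.142, 2.5% |
| 80/20 | 1.5 | 0.791, 12.1% | 1.265, 1.3% |

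With equal SDs, R = 1 at every split. In these formulae R depends on the split and the SD ratio, not on N; repeating the calculation at N = 240 changed the sizes by less than 0.001. Interval coverage mirrors size: 100 − 7.0 = 93.0% at 60/40 and 100 − 12.1 = 87.9% at 80/20, in the adverse direction at ratio 1.5.

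**Simulation check.** An ANCOVA with one baseline covariate was simulated (N = 400, 3,000 replicates, splits 200/200, 133/267 and 100/300), with normal residuals at SD ratios 0.5 to 2 and with a zero-inflated score.

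- Across all settings the pooled-variance test rejected in 0.8% to 15.3% of null samples, and HC3 in 4.3% to 6.2%.
- For the zero-inflated score at 133/267, the pooled test gave 9.2% when the smaller group had the larger SD (1/0.62, about 1.6 times) and 2.3% when the larger group had it (1.60 times). HC3 gave 5.6% and 4.4%.
- With equal variances and normal residuals, pooled and HC3 gave 5.1% and 4.9% at 200/200, and 4.6% and 4.8% at 100/300.
- Mean-centred Levene's test on zero-inflated residuals with equal variances rejected in about 21% of samples, against a nominal 5%.

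The covariate in these runs was independent of group. The trial's covariates are to be chosen partly because they differ between groups, so these figures are indicative.

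**The case against.** The strongest objection is that the article only leaves something unsaid. It is a condensed publication, and what follows a variance check is often settled in the full protocol or analysis plan, neither of which is shown. That stands as far as it goes: a reader might infer that Levene's result will be ignored, but the article says only that the check is made. The point nevertheless rests on a stated choice. ANCOVA is the sole method named for the primary outcome, while latitude is written for the secondary ones. A rule triggered by Levene's test would also be a weak safeguard on a skewed score, as the 21% false rejection rate shows.

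The second objection is that neither unequal sizes nor unequal variances is documented. This is correct. The Discussion speaks of characteristics, needs and motivation; it does not predict different S-STS levels, still less different residual variances after adjustment. Covariates in the model may reduce any difference in spread. Both conditions are plausible, and both are needed.

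The third is that self-selection is the larger problem in a non-randomised pilot, and the article already acknowledges bias from patient choice. That also stands. A correctly sized test would still not isolate the effect of the contact schedule. It limits the importance of this point, but does not justify intervals with the wrong coverage.

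**Conclusion.** The point holds conditionally. As published, the primary analysis has no stated protection against unequal residual variances in groups whose sizes are left to patient choice. At a 60/40 split with an SD ratio of 1.25 to 1.5 the distortion is modest: a true size of 6.1-7.0% or 4.1-3.4%, depending on which group is more variable. At 80/20 it is material: 8.6-12.1% or 2.5-1.3%. These splits and ratios are assumptions; the article supplies only the alpha level and the target of 400.

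A reader might go further and infer that the primary test has an inflated false-positive rate. The documents do not support that. The error can run either way, and it disappears with equal groups or equal variances. The importance is moderate at most: this is a pilot without a power calculation, and the correction concerns error bars, not the bias in the estimate from self-selection.

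**What to change.** In Primary outcome measures, state that the ANCOVA group difference in S-STS is reported with heteroscedasticity-consistent (HC3) standard error, 95% confidence interval and p-value, whatever Levene's test shows. In Statistical analysis, label Levene's test as descriptive. In Secondary outcome measures, apply the same rule to group comparisons actually made by AN(C)OVA; the other listed methods need no change on this account.

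The model and the point estimate stay the same. The cost is a sentence or two, a check that the chosen software produces HC3 output, and a negligible loss of efficiency when variances are equal. HC3 is not exact: its highest simulated rate was 6.2%, for a zero-inflated score at 100/300 with the smaller group more variable, where the pooled test gave 12.6%. The text should also say that this change does not address confounding by patients' choice of group.
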